### Measurements

All the variables that will be recorded for each one of the patients included in the study are summarized in Additional file 1: Table S1.

Characteristics recorded at the time of transplantation include donor and recipient age and gender, body weight, height, body mass index (weight in kilograms divided by the height in meters squared), primary cause of renal failure (type I diabetes mellitus, type II diabetes mellitus, primary glomerulonephritis, nephrosclerosis including hypertension and renovascular disease, polycystic kidney disease, systemic lupus erythematosus, and others), cold ischemia time, type of dialysis prior to transplant (hemodialysis or peritoneal dialysis), total duration of renal replacement therapy before transplantation, and previous transplants. The date of transplantation and the type of donor (a deceased or living donor) will also be recorded.

Information about other traditional cardiovascular risk factors at the time of transplantation will also be collected, including history of tobacco smoking, hypertension, hypercholesterolemia, left ventricular hypertrophy, prior diabetes and a history of cerebrovascular disease (transient ischemic attacks and strokes), peripheral vascular disease (revascularization procedures and amputations) and malignancies prior to transplantation.

After transplantation, episodes of acute rejection and infections will be registered, together with the patient's smoking status, new-onset diabetes and diagnosis of left ventricle hypertrophy. Biochemical parameters will be collected during the post-transplantation follow-up at week 1, week 2, month 1, month 3, month 6, and yearly thereafter. These will include white blood counts, hematocrit, haemoglobin, cholesterol, high-density lipoprotein (HDL) cholesterol, low-density lipoprotein (LDL) cholesterol, triglycerides, creatinine levels and 24-hour proteinuria. At the same time intervals, systolic and diastolic blood pressure will be recorded. Renal function will be estimated using the Cockcroft-Gault formula [37] and the modified Modification of Diet in Renal Disease (MDRD) equation [38]. In the analysis of factors predicting new post-transplant cardiovascular events, the average of laboratory and blood pressure values recorded before the event will be considered.

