For the analysis, the cut-points defining the control of each risk factor will be taken from the European Guidelines on CVD prevention [39]. For estimates of dyslipidemia control based on LDL, HDL cholesterol and triglycerides, we will use the cut-points agreed in the consensus statement from the American Diabetes Association and the American College of Cardiology Foundation [40].

The initial immunosuppressive regimen of the patients and changes in treatment during follow-up will be recorded. Dosage of immunosuppressive drugs will also be registered after transplantation at week 1, week 2, months 1, 3 and 6, and yearly thereafter. The use of antihypertensive and lipid-lowering drugs after transplantation will also be registered at the same times.

Post-transplant cardiovascular events are defined as the presence of myocardial infarction, invasive coronary artery therapy, cerebral vascular events (stroke and transient ischemic attacks), new-onset angina, congestive heart failure, rhythm disturbances (ventricular tachycardia, atrial fibrillation and the need for a pacemaker), and peripheral vascular disease. Peripheral vascular disease is defined as the need for invasive therapy or conservatively managed limb gangrene.

Patients will be followed-up from the date of renal transplantation until death or their return to dialysis.

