### Sample size

During the study period (1981-2008) n = 2059 kidney transplants were performed in the A Coruña Hospital, corresponding to 1794 patients.

This sample size will make it possible to detect as significant, in a Cox regression model, a relative risk of 1.33 or more associated with a prevalence of exposure to a cardiovascular risk factor of 50% and a censored data percentage of 78% (Security: 95%; Statistical power: 80%). Assuming an exposure prevalence of 50% maximizes the sample size necessary to detect a relative risk of this magnitude. According to previously published data for this cohort of patients, the estimated incidence of CVD at five years is 22.2% [47], and so the censoring value was estimated at 78%. In this situation, the sample size required to estimate a relative risk of 1.33 or more (α = 0.05, β = 0.2) would be n = 1755 patients.

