### Statistical analysis

A descriptive analysis of the variables recorded will be performed. Observed frequencies and percentages will be used for qualitative variables, with their 95% confidence interval, and the mean and standard deviation or median and interquartilic range for quantitative variables.

The primary outcome for this study will be the estimation of the probability of cardiovascular disease in the presence of other competitive events in renal transplant patients. The cumulative incidence of cardiovascular events after kidney transplantation will be analyzed by competing risk survival methods, where each subject is at risk of failure from different causes. Therefore, each patient will be classified in four states of interest (alive with functioning graft, death, graft failure and cardiovascular disease).

Cumulative incidence functions will be used to compare the observed incidence of events between groups [48]. The cumulative incidence function regression model of Fine and Gray will be used for multiple regression analyses [49]. Additionally, the clinical relevance of different variables will be evaluated using the ARR (Absolute Risk Reduction), RRR (Relative Risk Reduction) and NNT (Number Needed to Treat).

In order to analyze the ability of each of the four cardiovascular risk scores to predict cardiovascular events rates, the concordance c index [50] and the area under the receiver-operating characteristic (ROC) curves, using a time-dependent approach [51], will be calculated. To calibrate the scores, relative risk ratios for observed-to-predicted event rates will be computed, and the Hosmer-Lemeshow test will be applied.

Based on the competing risks analysis, a nomogram to estimate the probability of cardiovascular events after kidney transplantation will be developed. The objective is to use the conditional cumulative incidence function to provide a patient-specific prediction of the probability of failure in the setting of competing risks.

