The predictive performance of the nomogram will be evaluated by assessing both discrimination and calibration values [52]. A bootstrap re-sampling approach with 1000 replications will be used to reduce overfit bias. Discrimination will be quantified with the concordance c index and the area under the receiving operating characteristic (ROC) curve [50,51]. The nomogram will then be calibrated graphically, comparing the predicted probabilities with the actual rate of patients with cardiovascular events. A Loess curve will be fitted to the data and compared with an ideal fit. In addition, the Brier score will be calculated as a measure of the predictive accuracy of the model.

A p-value of < 0.05 will be considered as statistically significant (two-sided). Statistical analyses will be carried out with SPSS version 17.0 (SPSS Inc., Chicago, IL.) and R version 2.9.1 (The R Foundation for Statistical Computing), adding the ROCR, Design and Hmisc libraries.

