## Discussion

In recent years, several important changes have occurred in the management of kidney transplant patients that have been associated with an improvement in rejection rates and early graft survival [53]. Therefore, attention is now focusing on improving long-term transplant outcomes [3]. Renal dysfunction and increased cardiovascular risk are some of the factors that have a negative impact on long-term graft and patient survival. Although some authors have documented a reduction in CVD-related deaths in kidney transplant recipients in recent years, CVD is still the leading cause of death in patients with a functioning allograft [2].

Several studies have analyzed the risk factors connected with the incidence of cardiovascular events after kidney transplantation [4-29]. However, the role of some novel risk factors remains unclear. Furthermore, most of the previous studies are based on retrospective analyses of registry data, which contains information only on baseline data at the time of transplantation and the immediate post-transplantation follow-up. As a result, long-term follow-up data on clinical, biochemical and treatment covariates after transplantation is not always available.

This study will allow us to determine the post-transplant incidence of cardiovascular events in a cohort of renal transplant recipients in Spain, as well as to confirm the relationship between some CVD risk factors and the occurrence of a cardiovascular event in these patients. The development of a specific CVD risk score for kidney transplant recipients would make it possible to identify patients at high risk for coronary events at the time of transplantation, or shortly after the transplant. Therefore, this risk assessment could be used to recommend lifestyle changes for patients, to initiate appropriate treatment, or to redesign the immunosuppressive regimens for the prevention of primary or recurrent cardiovascular events in kidney transplant patients. The majority of studies use survival analysis strategies with the methodology of Kaplan and Meier. As this methodology may lead to overestimating the likelihood of the occurrence of the events of interest, we propose a competitive risk analysis in order to study the prognosis of these patients [48,49].

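### Laboratory and blood-pressure predictors are averaged up to the event, so as fixed covariates they depend on event time and can bias associations for markers that change after transplantation

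*Protocol article*

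**What the plan says.** The protocol article (Measurements) has laboratory values and blood pressure recorded "at week 1, week 2, month 1, month 3, month 6, and yearly thereafter": five occasions in the first half-year, then one a year. For the analysis of factors predicting new events, "the average of laboratory and blood pressure values recorded before the event will be considered". The same section sets follow-up: "Patients will be followed-up from the date of renal transplantation until death or their return to dialysis". Its length therefore differs between patients.

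Statistical analysis names one multivariable method: "The cumulative incidence function regression model of Fine and Gray will be used for multiple regression analyses". The article mentions no time-updated covariate, no landmark and no fixed averaging window. It does not say which values are averaged in patients who never have an event. The Discussion wants the new score to identify high-risk patients "at the time of transplantation, or shortly after the transplant".

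**The concern.** For a patient with an event, the event itself decides which measurements enter the predictor. An early event leaves only early post-operative values. A patient who stays event-free for years is represented mainly by later ones, if the average runs over all follow-up. The covariate is then built from information that arises after time zero, and its content depends on the outcome time that the model is meant to explain.

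If a marker's mean moves with time since transplantation, this average partly measures time spent event-free. A marker that falls after surgery looks harmful, and one that rises looks protective, even with no effect on cardiovascular risk. Real effects are shifted too. Factors related to post-transplant events are part of the first objective, and the article presents long-term post-transplant covariate data as something many earlier studies lacked. A larger cohort makes a false association of this kind more certain.

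**Working it through.** **The plan's own figure.** Sample size gives 1755 patients for a relative risk of 1.33, with 50% exposure, 78% censoring, two-sided 5% and 80% power. Schoenfeld: events = (1.960 + 0.842)² / (0.25 × ln(1.33)²) = 386.0; patients = 386.0 / 0.22 = 1754.7, i.e. 1755. The figure reproduces. It does not depend on how a predictor is built, so it neither supports nor answers the point.

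**The mechanism in two patients.** Assume a no-effect marker with an early excess of 1 between-patient SD, decaying as exp(-t/0.15) with t in years. The expected excess at week 1, week 2, month 1, month 3, month 6 and year 1 is 0.880, 0.775, 0.574, 0.189, 0.036 and 0.001, and about 0 afterwards.

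- Event at month 4: four values, (0.880 + 0.775 + 0.574 + 0.189) / 4 = 0.60 SD.
- Event-free with visits through year 10: fifteen values, (2.418 + 0.036 + 0.001) / 15 = 0.16 SD.

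Two patients with the same underlying level differ by about 0.44 SD only because one had an early event.

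**Simulation inputs.** From the article: 1794 patients, 22.2% five-year incidence, the visit schedule, two-sided 5%. Assumed: competing hazard 5% per year; constant hazards, which make the cardiovascular hazard 0.0574 per year; between-patient SD 1 and within-patient SD 0.7; follow-up either uniform over 1-28 years or fixed at 5 years; the form and size of the trend. The average of values up to the event or end of follow-up enters as a fixed covariate. There are 400 cohorts per row, so the Monte Carlo standard error at 5% is √(0.05 × 0.95 / 400) = 1.1 percentage points.

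Fine-Gray results for a marker with no effect:

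| Trend after transplantation | p < 0.05, 1-28 y | p < 0.05, 5 y | Spurious sHR per SD (1-28 y / 5 y) |
|---|---|---|---|
| None | 5.5% | 6.0% | 1.00 / 1.00 |
| Early excess 0.25 SD | 7.7% | 9.0% | 1.02 / 1.02 |
| Early excess 0.5 SD | 13% | 17% | 1.03 / 1.05 |
| Early excess 1 SD | 34% | 42% | 1.06 / 1.09 |
| Early excess 2 SD | 87% | 94% | 1.13 / 1.19 |
| Early deficit 1 SD | 37% | 42% | 0.94 / 0.92 |
| Rise of 0.05 SD per year | 30% | 7% | 0.95 / 0.98 |

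Further runs under other assumptions (for example within-patient SD 1 and a settling constant of 0.2 year) widen the ranges to 34-56% at 1 SD and 87-96% at 2 SD.

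**A marker with a real effect.** With a true sHR of about 1.26 per SD (Fine-Gray, both SDs 1, follow-up 1-28 years), the estimate was 1.17 or 1.09 if the marker rose by 1 or 2 SD after surgery, and 1.35 or 1.43 if it fell by 1 or 2 SD. Across all runs the 2 SD cases span 1.03-1.11 (rise) and 1.41-1.53 (fall).

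**Definitions that do not use the outcome.** For the same no-effect markers, false-positive rates were:

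- First post-transplant value, Fine-Gray: 2.5-6.0%.
- Mean to month 6, Fine-Gray from a 1-year landmark: 3.3-7.0%; from a 6-month landmark: 3-7%.
- Running mean updated over time, cause-specific Cox: 4-7% (100 runs per scenario, trend scenarios only).

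Hazard ratios were about 1.00 throughout.

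**The case against.** **The article does not say how the average enters the model.** A running mean, updated at each event time for everyone still at risk, is one possible reading, and it would be close to nominal. A condensed article may also leave covariate coding to a fuller plan. But this sentence is a stated rule. It speaks of a single average, nothing mentions updating, and Fine-Gray, the only named regression, suits covariates measured during follow-up poorly because patients stay in its risk set after a competing event. If a running mean is meant, the text has to say so.

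**The window for event-free patients is inferred.** This stands. However, a fixed window for those patients alone would still leave the event patients' window set by the outcome.

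**The bias needs a time trend.** This stands, and trends of 0.25-0.5 SD inflate the error rate only modestly. The article gives no trajectories. It does plan to record drug doses and treatment at the same visits, and its Discussion acknowledges treatment changes during follow-up, so stable means cannot be taken for granted. Adjusting for year of transplantation, as the Discussion plans, handles calendar time and not time since surgery.

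**Guideline cut-points will define risk-factor control.** Dichotomising reduces the problem without removing it. With a median split as a stand-in, false positives were 27-32% at 1 SD and 73-80% at 2 SD.

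**Stronger readings.** A reader might infer that no-effect markers in general will emerge as significant risk factors, that real effects are always diluted, or that the main incidence result is compromised. The documents support none of these: without drift the error rate stays near 5%, the direction follows the drift, real effects can be inflated as well as diluted, and incidence does not use these averages. Nor does losing patients whose event precedes the week-1 visit matter: under the constant hazards this is 0 to 6 of 1794.

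**Conclusion.** The rule is wrong as written for post-transplant laboratory and blood-pressure predictors, because it lets the outcome set the averaging window of a covariate destined for a Fine-Gray model. The harm is conditional on a marker's mean changing after transplantation, and its size for any given marker cannot be read from the article. On the assumptions above it runs from none (no drift) to a near-certain false association (2 SD early excess). Slow drift depends strongly on length of follow-up.

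The scope is limited to laboratory and blood-pressure factors within the risk-factor part of the first objective, and to the new score if it uses these averages. In that case there is a further difficulty: an average up to the event is not known at the time the Discussion wants the score applied. The overall cumulative incidence, the four established scores (calculated at transplantation) and the baseline donor, recipient and dialysis factors are untouched.

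**What to change.** Replace the sentence in Measurements with two rules.

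1. Risk-factor analysis: enter each laboratory and blood-pressure variable as a time-updated covariate in a cause-specific Cox model. At each event time use the mean (or last value) of measurements recorded up to then, for every patient still at risk.
2. Fine-Gray models, cumulative-incidence comparisons and the nomogram: use baseline values, or the mean up to a fixed landmark (for example 6 months) among recipients still event-free and under follow-up at that date, with time counted from the landmark.

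The cost is revised wording and a start-stop or landmark dataset built from visits already planned. The 6-month landmark gives up early events. With the hazards above, the six-month incidence is (0.0574 / 0.1074) × (1 - exp(-0.1074 × 0.5)) = 0.0279, so about 0.0279 × 1794 = 50 events are lost, against roughly 0.22 × 1794 = 395 over five years. A constant hazard is assumed; more would be lost if events cluster early. The time-updated model avoids this landmark loss.

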**Methods/Design:**

Observational prospective cohort study of all kidney transplant recipients in the A Coruña Hospital (Spain) in the period 1981-2008 (2059 transplants corresponding to 1794 patients).

The variables included will be: donor and recipient characteristics, chronic kidney disease-related risk factors, pre-transplant and post-transplant cardiovascular risk factors, routine biochemistry, and immunosuppressive, antihypertensive and lipid-lowering treatment. The events studied in the follow-up will be: patient and graft survival, acute rejection episodes and cardiovascular events (myocardial infarction, invasive coronary artery therapy, cerebral vascular events, new-onset angina, congestive heart failure, rhythm disturbances and peripheral vascular disease).

Four cardiovascular risk scores were calculated at the time of transplantation: the Framingham score, the European Systematic Coronary Risk Evaluation (SCORE) equation, and the REGICOR (Registre Gironí del COR (Gerona Heart Registry)), and DORICA (Dyslipidemia, Obesity, and Cardiovascular Risk) functions.

The cumulative incidence of cardiovascular events will be analyzed by competing risk survival methods. The clinical relevance of different variables will be calculated using the ARR (Absolute Risk Reduction), RRR (Relative Risk Reduction) and NNT (Number Needed to Treat).

The ability of different cardiovascular risk scores to predict cardiovascular events will be analyzed by using the c index and the area under ROC curves. Based on the competing risks analysis, a nomogram to predict the probability of cardiovascular events after kidney transplantation will be developed.

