This project was designed with three main objectives: firstly, to determine the incidence of post-transplant cardiovascular events after renal transplantation and related factors; secondly, to examine the ability of established cardiovascular risk scores (Framingham, Regicor, SCORE, and DORICA) to predict post-transplantation cardiovascular events in renal transplant recipients; and finally, to develop and validate a cardiovascular risk score to predict the risk of developing a cardiovascular event after kidney transplantation.

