### Quantification of cardiovascular risk

Four established cardiovascular risk scores will be applied to the kidney transplant recipients at the time of transplantation: the Framingham risk factor score, the European Systematic Coronary Risk Evaluation (SCORE) equation, and two coronary risk equations that use the calibrated Framingham functions for the Spanish population, the REGICOR (Registre Gironí del COR (Gerona Heart Registry)) and DORICA (Dyslipidemia, Obesity, and Cardiovascular Risk) functions.

The Framingham risk score will be calculated using both the classic Framingham-Anderson equation [30] and the equation modified by Wilson [31]. These scores predict the risk of developing fatal or non-fatal coronary heart disease (CHD) within a 10-year time period in adults between the ages of 30-74 with no known previous history of CHD, stroke, or peripheral vascular disease. CHD includes angina pectoris, myocardial infarction, coronary insufficiency (unstable angina) and coronary heart death.

The original Framingham-Anderson equation includes the following risk factors: age, sex, systolic blood pressure, total cholesterol, HDL-cholesterol, diabetic status, tobacco smoking status and evidence of left ventricular hypertrophy on resting electrocardiogram (ECG). The Framingham-Wilson equation replaces the continuous measurements of systolic blood pressure, total cholesterol and HDL-cholesterol with categorical variables based on the risk categories of the Joint National Committee on Blood Pressure and the National Cholesterol Education Program (NCEP) [41-43]. It also takes into account information regarding diastolic and LDL-cholesterol levels, and does not include the diagnosis of left ventricular hypertrophy due to its high association with hypertension and the absence of standard, universally accepted ECG criteria.

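### Stopping follow-up at return to dialysis suits the competing-risks primary outcome, but not patient survival or the calibration of the 10-year risk scores

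*Protocol article*

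**What the plan says.** - **Measurements** sets the end of follow-up: "Patients will be followed-up from the date of renal transplantation until death or their return to dialysis". No other section extends it.
- **Statistical analysis** defines the primary outcome as "estimation of the probability of cardiovascular disease in the presence of other competitive events in renal transplant patients", and says that "each patient will be classified in four states of interest (alive with functioning graft, death, graft failure and cardiovascular disease"). Graft failure therefore sits beside death and CVD as an end state.
- **Background** words the first objective as "to determine the incidence of post-transplant cardiovascular events after renal transplantation and related factors", with no restriction to time with a working graft.
- **Abstract, Methods/Design** adds patient survival: "The events studied in the follow-up will be: patient and graft survival, acute rejection episodes and cardiovascular events".
- **Quantification of cardiovascular risk** says of the Framingham equations: "These scores predict the risk of developing fatal or non-fatal coronary heart disease (CHD) within a 10-year time period". SCORE is described there as a 10-year risk of fatal CVD. Neither target depends on graft status.
- **Statistical analysis** calibrates the scores with observed-to-predicted event rates and a Hosmer-Lemeshow test. It does not say how a patient who returns to dialysis before 10 years is counted.
- **Design and study population** includes repeat transplants, and **Sample size** counts 2059 transplants in 1794 patients.

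**The concern.** Losing a graft does not prevent a cardiovascular event or a death. A recipient who returns to dialysis in year 3 and has an infarction in year 5 contributes no CVD event to that transplant's record. This matters for two results.

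**Patient survival.** Only death with a functioning graft is observed. A survival curve censored at graft loss is too favourable if mortality is higher on dialysis.

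**Score calibration.** A score predicting risk over 10 years whatever happens to the graft would be compared with an observed rate whose collection ends at graft loss. If that rate is too low, the observed-to-predicted ratio is pulled down. The Background reports that Framingham underestimates risk in these patients, and a depressed ratio could hide exactly that.

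Both effects come from a data-collection rule, so later analysis can only replace the missing follow-up with assumptions.

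**Working it through.** **The plan's own figure.** The required 1755 patients reproduces: (1.960 + 0.842)² / (0.25 × ln(1.33)²) = 386.04 events, and 386.04 / 0.22 = 1754.7. The follow-up rule does not alter it.

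**Inputs.** From Sample size: five-year CVD incidence 22.2%, read here as cumulative incidence with graft failure and death competing (the article does not say so). Everything else is assumed, because the article gives no figures:
- constant hazards
- death without CVD, d = 0.015 per year
- graft loss, g = 0.02, 0.03 or 0.05 per year
- after graft loss, CVD hazard k·c and death hazard m·d, with (k, m) = (1, 1) or (2, 3).

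**Step 1: CVD hazard c.** Solve c/(c+d+g) × (1 − exp(−5(c+d+g))) = 0.222. This gives c = 0.0552, 0.0566 and 0.0597.

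**Step 2: graft loss terminal.** The 10-year incidence is c/(c+d+g) × (1 − exp(−10(c+d+g))). For g = 0.03: 0.0566/0.1016 × (1 − exp(−1.016)) = 35.6%.

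**Step 3: graft loss censored, death competing.** The 10-year incidence is c/(c+d) × (1 − exp(−10(c+d))). For g = 0.03: 0.0566/0.0716 × (1 − exp(−0.716)) = 40.4%.

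**Step 4: complete follow-up.** Add to Step 2 the integral over s from 0 to 10 of g·exp(−(c+d+g)s) × kc/(kc+md) × (1 − exp(−(kc+md)(10−s))).

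| 10-year CVD incidence | g = 2% | g = 3% | g = 5% |
|---|---|---|---|
| Graft loss terminal | 36.3% | 35.6% | 34.1% |
| Graft loss censored | 39.6% | 40.4% | 42.0% |
| Complete, hazards unchanged | 39.6% | 40.4% | 42.0% |
| Complete, CVD ×2 and death ×3 | 41.5% | 43.1% | 46.2% |

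**Step 5: relative shortfall against complete follow-up.**

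| Handling of graft loss | Hazards unchanged | CVD ×2, death ×3 |
|---|---|---|
| Terminal | 8%, 12%, 19% | 12%, 18%, 26% |
| Censored | 0%, 0%, 0% | 4%, 6%, 9% |

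An observed-to-predicted ratio shrinks by the same proportion, if the score's own endpoint behaves like the CVD composite used here.

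**Wider graft-loss range.** The rates used imply about 8-19% graft failure as first event at five years. If that figure is instead 10%, 20% or 30%, with death without CVD at 1-2% per year and both hazards after graft loss 1 to 2 times those before, terminal handling multiplies the 10-year ratio by about 0.84-0.90, 0.71-0.80 or 0.60-0.70.

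**Step 6: patient survival.** Assume mortality μ = 0.02 per year with a functioning graft, doubled on dialysis. Censoring at graft loss gives exp(−0.2) = 81.9% at 10 years. True survival is exp(−10(μ+g)) plus the integral over s from 0 to 10 of g·exp(−(μ+g)s) × exp(−2μ(10−s)), which is 80.4%, 79.8% and 78.6%. With equal mortality before and after graft loss, the gap is zero.

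**The case against.** The strongest reply is that the follow-up rule and the primary analysis agree. A reader might infer that the study's main CVD incidence is understated. The article does not support that: the primary outcome is declared as a competing-risks probability with graft failure as its own state, and that quantity needs nothing observed after graft loss. This part of the reply stands in full. Preferring CVD regardless of graft status for the primary aim would be choosing a different estimand.

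A reader might also infer that events after graft loss are never collected, or that only the first graft is studied. Neither follows. Repeat transplants are included, so a re-transplanted patient can re-enter. The clear loss is events in the dialysis interval and in patients who are never re-transplanted.

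Nor does the article say that events after graft loss count as non-events in the calibration. If graft loss is censored and hazards do not change, the shortfall disappears. The 8-19% therefore comes wholly from terminal handling, not from the collection stop itself. This also stands, but censoring assumes that graft loss carries no information about CVD risk. The Background names graft function, proteinuria and rejection as CVD factors, and these plausibly drive graft loss too.

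Finally, patient survival is listed among the events studied but is not one of the three objectives, so its weight is modest.

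**Conclusion.** The concern holds for two stated uses and not for the primary outcome. All-cause patient survival cannot be properly estimated under the stated rule. The example overstates it by about 1.4 to 3.3 percentage points at 10 years, and only if mortality on dialysis is higher. The 10-year calibration compares scores that have no graft-loss exit with follow-up that has one. The size of the error depends on a handling rule the article does not state: 8-26% under terminal handling and 0-9% under censoring across the two scenarios, with graft loss at 2-5% per year. The bias due to the collection stop alone is the smaller of these. Every rate except the 22.2% is an assumption, so the figures show direction and plausible order, not an estimate for this cohort. The sample size is unaffected.

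**What to change.** 1. In Measurements, extend record review beyond return to dialysis for two items only, first cardiovascular event and death, up to death, last contact or a study closing date. Record return to dialysis as a dated intermediate event.
2. Use these data for the calibration of the 10-year scores, with death as the only competing event, and for patient survival.
3. Keep the four-state analysis as primary, and label its result as CVD with a functioning graft.
4. Where later records cannot be obtained, censor at last contact and restate the survival and calibration results as applying with a functioning graft. That wording should make clear that the scores' own target is wider.

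The cost is additional abstraction for patients who lost a graft. The Discussion says that data come mostly from hospital records, so no new patients or procedures are needed. The article does not give the number of patients involved, and records reach back to 1981. Where care moved elsewhere, some informative censoring will remain.
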